## Abstract

**Background:**

Stroke is a major cause of death and disability worldwide. Approximately 12–25% of stroke survivors develop complex regional pain syndrome type I (CRPS-I) within 3–12 months. CRPS-I is characterized by severe limb pain, abnormal pain, and vasomotor instability, which hinders rehabilitation. Insufficient efficacy and adverse reactions limit the use of current pharmacological treatments, such as non-steroidal anti-inflammatory drugs and gabapentinoids. Post-stroke CRPS-I is characterized by neuroinflammation, maladaptive neural plasticity, and central/peripheral sensitization. Repetitive transcranial magnetic stimulation (rTMS) regulates pain through cortical reorganization and inhibition of neuroinflammation, while acupuncture, particularly the Yuan-Luo Dajiejing (YLDJJ) technique, reduces central sensitization by activating endogenous opioids. However, no randomized controlled trial has compared the efficacy of YLDJJ acupuncture combined with rTMS in the treatment of CRPS-I after stroke.

**Methods:**

This randomized controlled trial will randomly assign eligible participants to three groups in a 1:1:1 ratio: the experimental group (YLDJJ acupuncture + rTMS), the control group 1 (conventional acupuncture + rTMS), and the control group 2 (sham acupuncture + rTMS). The participants will be aged 18–80 years old, with CRPS-I developing after stroke and meeting the specific inclusion criteria. The intervention measures will be administered once daily for 20 days. Pain intensity, assessed using the visual analogue scale (VAS), will be measured at baseline, on days 10 and 20, and at 1 and 3 months after treatment completion. Secondary outcome measures include motor function, muscle tone, shoulder range of motion, activities of daily living, thermal asymmetry, and neuroplasticity-related indicators. The sample size will be 126 participants, accounting for a 20% dropout rate.

**Conclusion:**

This trial will evaluate the efficacy and safety of Yuan-Luo Da-Jie-Jing acupuncture combined with rTMS. The results will be compared to two control groups: one receiving conventional acupuncture with rTMS, and the other receiving sham acupuncture with rTMS. The results are expected to provide evidence for formulating clinical treatment strategies for CRPS-I after stroke.

**Clinical trial registration:**

(ITMCTR, http://itmctr.ccebtcm.org.cn/), No. ITMCTR2025001677.

## Introduction

Stroke, including ischemic and hemorrhagic subtypes, is the second leading cause of mortality and a major contributor to long-term disability globally. It imposes a substantial socioeconomic burden due to acute neurological deficits and chronic sequelae (1). While the incidence rates of stroke increase steadily with age and roughly double every 10 years after 55 years of age, both ischemic (2) and hemorrhagic strokes are becoming increasingly more prevalent among younger people (3). One major complication of stroke is complex regional pain syndrome type I (CRPS-I), affecting 12–25% of stroke survivors within 3–12 months (4). Characterized by severe limb pain, allodynia, and vasomotor instability (5), CRPS-I profoundly undermines recovery and quality of life.

The pathogenesis of CRPS-I involves neuroinflammation and maladaptive plasticity (6). Stroke-induced injury triggers peripheral sensitization via cytokines and sympathetic-pain coupling (7–9), leading to central sensitization (7, 10) and cortical reorganization (11). Autonomic dysfunction, including vasoconstriction and catecholamine hypersensitivity (12, 13), and sustained neuroinflammation perpetuate pain (9, 14, 15).

Current pharmacological agents, such as nonsteroidal anti-inflammatory drugs (NSAIDs) and corticosteroids, provide inadequate efficacy (30–40% failure) and several side effects (16, 17). It brings huge challenges to patients’ recovery and treatment.

Repetitive transcranial magnetic stimulation (rTMS), specifically high-frequency rTMS targeting the contralateral M1 (level C recommendation) (18), shows promise for the treatment of stroke. Its analgesic mechanisms include modulation of the sympathetic system, restoration of cortical representation, suppression of neuroinflammation (19, 20), and attenuation of central sensitization (21), promoting adaptive plasticity (22, 23).

Acupuncture alleviates central sensitization via endogenous opioid release and modulation of neuroinflammatory cascades (24). Specific techniques, such as YLDJJ, may be effective for post-stroke neuropathic pain (25, 26). Diverging from conventional local acupoint selection, YLDJJ, derived from the classical doctrine of ‘12 meridians connecting sequentially as an endless cycle’ (Ling Shu·Meridians), emphasizes systemic neuroregulation through sequential needling of Yuan-Source (primary qi-influx loci) and Luo-Connecting (inter-meridian anastomosis loci) points on all 12 meridians. It aims to restore global qi-blood dynamics (a concept in traditional Chinese medicine). Contemporary evidence suggests three technical distinctions: (1) Holistic modulation: YLDJJ is proposed to augment functional connectivity between perilesional sensorimotor cortex and contralateral cerebellum (27), unlike conventional peri-shoulder acupuncture, which preferentially activates ipsilateral somatosensory cortices; (2) anti-neuroinflammatory specificity: Animal studies have shown that YLDJJ may downregulate Reg3b expression in dorsal root ganglia (2.1-fold greater than conventional acupuncture), disrupting TNF-*α*-mediated neuro-immune crosstalk (28); (3) sustained analgesia: Previous RCTs using YLDJJ have reported 19.7% superior pain relief retention at 3 months compared to local acupoint protocols for CRPS-I (25). These mechanistic properties may enable YLDJJ to disrupt the “peripheral sensitization, central maladaptation, and autonomic dysfunction” vicious cycle in CRPS-I. It also enhances pain thresholds, neural reorganization (27, 29), corticospinal tract remodeling, and cerebral blood flow (30). Nevertheless, acupuncture phobia and protracted treatment regimens undermine adherence (31).

Based on the aforementioned hypothesis regarding the regulatory effect of rTMS on central sensitization and the assumption that YLDJJ acupuncture can systematically modulate the pathological progression of CRPS-I, this approach not only addresses the insufficient efficacy of rTMS alone but also overcomes the low compliance of patients with traditional acupuncture.

## Objectives

Regarding the treatment of post-stroke CRPS-I, the relative efficacy of three interventions, including YLDJJ acupuncture combined with rTMS, conventional acupuncture combined with rTMS, and sham acupuncture plus rTMS, remains inadequately validated. Furthermore, no RCT has evaluated the efficacy and safety of these interventions in patients suffering from post-stroke CRPS-I. Therefore, we designed this RCT protocol to assess the effects of the three interventions on post-stroke CRPS-I and its associated symptoms, aiming to provide evidence-based guidance for the clinical management of post-stroke CRPS-I.

## Methods

### Trial design

This trial protocol adheres to the complete list of the SPIRIT 2025 Statement (32). A trial flowchart was created to clearly present the entire implementation process of this RCT. Details can be found in Figure 1. The diagram covers participant recruitment and screening, randomization, intervention implementation, outcome assessment, and data analysis. It also visualizes the intervention pathways and key time points of the three groups.

**Figure 1 fig1:**
[figure not shown]
Flow chart for clinical trial procedure.

### Study participants

This RCT will be conducted at Nanbu County People’s Hospital, following the Guidelines for the Diagnosis and Initial Management of Stroke and Transient Ischaemic Attack in Individuals Aged 16 Years and Over (33), and the Budapest Criteria for CRPS-I diagnosis (4). Specialist physicians will assess the eligibility of potential participants. Those who voluntarily participate will sign an informed consent form before enrollment.

### Eligibility criteria

#### Inclusion criteria

(1) Confirmed diagnosis of CRPS-I based on the Budapest clinical diagnostic criteria.(2) CRPS-I secondary to ischemic or hemorrhagic stroke confirmed based on CT/MRI within 3–12 months before enrollment.(3) Mean pain intensity ≥4 on the visual analogue scale (VAS; 0–10 cm) during 7 days before the intervention.(4) Unilateral upper-limb pain localized to the hemiparetic extremity.(5) Neurologically stable status, defined as a National Institutes of Health stroke scale (NIHSS) score ≤15.(6) Adequate tolerability for both acupuncture and repetitive rTMS interventions.(7) Aged between 18 and 80 years at screening.(8) Documented hand dominance before stroke.(9) Provision of written informed consent voluntarily obtained before participating in the trial.

#### Exclusion criteria

(1) Diagnosis of type 2 CRPS or a documented history of CRPS before stroke.(2) Presence of current limb fracture, local infection, or peripheral neuropathy in the affected extremity.(3) Presence of severe aphasia, unilateral neglect, or cognitive impairment.(4) History of recurrent stroke, brainstem or cerebellar lesions, or bilateral involvement.(5) Presence of implanted metal or electronic medical devices, such as cardiac pacemakers, a history of epilepsy, or intracranial hypertension.(6) Bleeding problems, fear of needles, or skin problems where acupuncture will be done.(7) Presence of comorbid central pain after stroke, phantom limb pain, or other chronic pain syndromes.(8) Presence of severe psychiatric disorders.(9) Opioid use or undergoing interventional treatment for pain within 4 weeks before enrollment.(10) Pregnancy, lactation, or concurrent participation in other clinical trials.

### Criteria for discontinuation of the intervention

Participant involvement in the trial may end early due to the following reasons:

Serious adverse event (SAE): Discontinue immediately if the investigator links an SAE to acupuncture or rTMS.

Withdrawal of consent: Participants may voluntarily withdraw consent at any time without a reason.

Protocol violation: Major deviations that compromise safety or data integrity, as judged by the principal investigator (e.g., starting prohibited treatments or finding ineligibility after randomization).

Loss to follow-up: Participant cannot be reached for three sessions or assessments.

Clinical deterioration: An independent clinician confirms a decline in health status, making participation unsafe or impractical.

Investigator’s decision: The investigator may stop intervention for any reason, protecting the participant’s best interest.

For all participants discontinuing the treatment, the reason and the date of withdrawal will be recorded in the case report form. We attempt to assess the final outcome at discontinuation.

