### Criteria for exclusion from analysis

All randomized participants will be included in the primary intention-to-treat (ITT) analysis. The criteria for the per-protocol (PP) population and data handling are mentioned in the following sections:

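### The protocol merges stopping treatment with leaving the trial, so scheduled outcomes that the intention-to-treat analysis needs may go uncollected for four avoidable reasons

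*Protocol article*

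**What the plan says.** The section is headed "Criteria for discontinuation of the intervention", yet its opening rule concerns the trial: "Participant involvement in the trial may end early due to the following reasons". The listed reasons include:

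- SAE: "Discontinue immediately if the investigator links an SAE to acupuncture or rTMS".
- Protocol violation, limited to major deviations as judged by the principal investigator, with these examples: "starting prohibited treatments or finding ineligibility after randomization".
- Clinical deterioration, which needs confirmation: "An independent clinician confirms a decline in health status, making participation unsafe or impractical".
- Loss to follow-up, defined by lack of contact: "Participant cannot be reached for three sessions or assessments".

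Withdrawal of consent and the investigator's decision complete the list. The last item speaks only of stopping the intervention, although it stands among the reasons for ending trial involvement.

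For everyone who discontinues treatment, the case report form takes a reason and a withdrawal date. The section closes: "We attempt to assess the final outcome at discontinuation". Nothing in the article says that scheduled visits go on after treatment stops.

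The next section states: "All randomized participants will be included in the primary intention-to-treat (ITT) analysis". The Outcomes section sets assessments at baseline, days 10 and 20, and 1 and 3 months after treatment. Primary outcome analysis estimates group differences at each time point. Both sections on missing data name MICE; the statistical one gives 20 imputed datasets. The robustness checks are comparisons with complete cases and with the per-protocol set.

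**The concern.** Stopping a treatment and leaving a study are different events. An intention-to-treat comparison needs outcomes from both those who finish treatment and those who do not. If assessment ends when treatment ends, the later VAS values of stoppers are missing because of a trial rule, when they could have been collected.

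The participants affected are not a random subset. Health decline, a treatment-related SAE or a change of pain medication (barred under Prohibited interventions, and so a possible major deviation) each plausibly relates to pain or tolerability. Imputed values then stand in for outcomes that may differ from those of people who stayed. At stake is whether the estimates at day 20, 1 month and 3 months describe all randomized participants.

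**Working it through.** **Step 1. Sort the six reasons by whether assessment is still possible.**

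- Assessment cannot continue: withdrawal of consent (where it covers follow-up) and loss to follow-up.
- Assessment can in principle continue: related SAE, major protocol violation, clinical deterioration, investigator's decision.

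The defect concerns the second group only.

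**Step 2. See which visits are at risk.** There are four visits after baseline. Someone who stops between days 10 and 20 and leaves loses three of them (day 20, 1 month, 3 months). Someone who stops before day 10 loses all four. A VAS taken on the day of stopping generally matches none of them.

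**Step 3. Ask whether the stated checks would reveal a problem.** Complete cases leave out participants with missing visits. Both definitions of the per-protocol set (Exclusion from PP analysis; Analysis populations) require a day-20 VAS, so anyone who stops earlier and leaves is absent from it. Neither comparison contains outcomes from after discontinuation, so neither tests a departure from missing at random.

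**Step 4. Size.** The plan's own dropout figure is reproduced first: 33 / (1 − 0.20) = 41.25, rounded up to 42 per group, and 3 × 42 = 126. The allowance is therefore 126 − 3 × 33 = 27 participants (0.20 × 126 = 25.2 before rounding). The article does not split it by arm or by reason.

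Let p be the proportion in an arm who stop and whose later visits are imputed, and δ the amount by which their true mean VAS exceeds the imputed mean. The bias in the difference between the experimental (E) and a control (C) arm has size

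p_E × δ_E − p_C × δ_C,

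which becomes (p_E − p_C) × δ when the departure is the same in both arms. All values of p and δ below are assumptions.

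| p_E | p_C | δ (points) | Bias (points) | Share of the 1.5-point MCID |
|---|---|---|---|---|
| 0.20 | 0.20 | 0.5 to 1.5, same in both arms | 0 | 0% |
| 0.25 | 0.15 | 0.5 | 0.10 × 0.5 = 0.05 | 3% |
| 0.25 | 0.15 | 1.0 | 0.10 × 1.0 = 0.10 | 7% |
| 0.25 | 0.15 | 1.5 | 0.10 × 1.5 = 0.15 | 10% |

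A less favourable assumption, with 20% stopping in the experimental arm and a departure in that arm only, gives 0.20 × 0.5 = 0.10 to 0.20 × 1.5 = 0.30 points.

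For scale, with the SD of 1.8 and 33 per group from the Sample size section, the standard error of a simple difference in means is √(2 × 1.8² / 33) = 0.44. A bias of 0.05 to 0.15 is then about 0.11 to 0.34 of a standard error.

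**The case against.** The text is softer than a fixed rule. Involvement *may* end, the heading names the intervention, and no sentence says that visits cease. Exclusion from PP analysis lists short exposure and eligibility violations separately from a missing day-20 VAS, which suggests that some of these participants are expected to have day-20 data. MICE details are referred to the statistical plan, which is not shown; the imputation model could use day-10 VAS, rescue use or the discontinuation VAS, and a sensitivity analysis away from missing at random could stand there. The illustrated bias is small.

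Much of this stands, and it limits the point. It does not remove it. The article speaks of trial involvement, records a withdrawal date for all who stop treatment, and plans a single final assessment at that moment. The word *may* leaves continued follow-up to case-by-case judgement. No imputation model can recover outcomes that were never collected.

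Three stronger readings are not supported:

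- A reader might infer that missing three of 20 sessions ends participation, in conflict with the 10-session threshold for the per-protocol set. The criterion is being unreachable, not failing to attend, and the threshold defines exposure for an analysis set. There is no conflict.
- A reader might infer that only withdrawn consent justifies ending follow-up. A participant who truly cannot be reached cannot be assessed either.
- A reader might treat the 20% dropout allowance as the number of participants whose data could be saved. It also covers withdrawn consent and true loss, and no split is given.

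**Conclusion.** The point holds for four reasons: related SAE, major protocol violation, clinical deterioration and investigator's decision. For these the article merges stopping treatment with leaving the trial and plans one attempted outcome at discontinuation. That conflicts with an analysis of all randomized participants at fixed visits up to 3 months.

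Bias is possible, not demonstrated. On assumed values it is 0.05 to 0.15 VAS points for a 10-percentage-point difference in discontinuation and a 0.5 to 1.5 point departure. It is zero if rates and departures are equal across arms, and larger if the departure is confined to one arm. A reader might infer that the plan overstates the benefit of the experimental treatment, but the documents give no arm-specific rates. The direction could also reverse, for example if prohibited analgesics lower the pain of those who stop. The change is worth making because it is cheap and because uncollected outcomes cannot be recovered later.

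**What to change.** Separate two events in the protocol and consent form: stopping the allocated treatment, and withdrawing from the study. Then:

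- For the four reasons above, keep the scheduled VAS and secondary assessments, with VAS by telephone where needed, unless the participant withdraws consent to follow-up or cannot be reached.
- Analyse these data in the randomized arm.
- Record the VAS at discontinuation as an additional value, not as a substitute for a scheduled visit.
- Record the date of stopping treatment and the date of leaving the study as separate items.

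The clinical criteria for stopping treatment are unchanged. The cost is protocol and consent wording, plus a few additional visits or calls from the existing schedule.

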### Exclusion from PP analysis

Participants will be excluded from the PP analysis if they undergo fewer than 10 intervention sessions (50% of the planned treatment) without a medically justified reason. They will be excluded because insufficient exposure prevents the assessment of treatment efficacy.

Major protocol violations that critically affect efficacy evaluation, such as incorrect randomization, receiving the wrong intervention group assignment, or violation of the key inclusion/exclusion criteria, will also lead to exclusion from PP analysis.

Additionally, missing the primary outcome (VAS score) at the post-treatment (day 20) time point results in exclusion from the PP analysis.

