#### Risk–benefit assessment

The potential benefits for participants and society include improved patient conditions and access to free medical care and condition assessments during the trial.

Risks to participants comprise treatment administration or withdrawal-related risks and the inherent risks of the disease. To protect participants’ health and interests during the trial, the researchers may discontinue the trial when necessary based on combination therapy/medication rules and discontinuation/withdrawal criteria, to protect participants’ health and interests.

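### The discontinuation rule can be read as ending follow-up when a participant starts a prohibited pain treatment or is found ineligible, leaving later VAS values uncollected

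*Protocol article*

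**What the plan says.** The section Criteria for discontinuation of the intervention opens with "Participant involvement in the trial may end early due to the following reasons". Six reasons follow. One is a major protocol deviation judged by the principal investigator to compromise safety or data integrity, with the examples "starting prohibited treatments or finding ineligibility after randomization". It stands beside withdrawal of consent and loss to follow-up, and no different consequence is given for it. For everyone who discontinues treatment, "the reason and the date of withdrawal will be recorded in the case report form", and then: "We attempt to assess the final outcome at discontinuation".

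Other sections bear on the point:
- Criteria for exclusion from analysis: "All randomized participants will be included in the primary intention-to-treat (ITT) analysis".
- Exclusion from PP analysis: "missing the primary outcome (VAS score) at the post-treatment (day 20) time point results in exclusion from the PP analysis". The PP definition under Analysis populations also requires the day-20 outcome.
- Prohibited interventions: all pain management apart from the permitted emergency relief, which is celecoxib.
- Table 4: VAS and an Additional treatment item at day 10, day 20, 1 month and 3 months.
- Both sections on handling missing data: multiple imputation by chained equations, compared with complete-case results.

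**The concern.** Stopping treatment and leaving the trial are different events, and the section does not keep them apart. An ITT analysis of all randomised participants needs outcomes from people who stop treatment or add another one. If the section is followed as a rule for leaving the trial, those outcomes are not measured.

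Starting a prohibited treatment is a sensitive trigger. Even with celecoxib available, people who turn to opioids, gabapentinoids or nerve blocks are likely to be in more pain than those who do not, and pain is the primary outcome. The loss could therefore depend on the outcome and differ between arms. Late-found ineligibility is covered by the same clause. It is not driven by pain, but it too could remove randomised participants from follow-up.

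This is not a detail that an analysis plan can settle later, because VAS values that were never collected cannot be recovered.

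**Working it through.** **1. The wording, side by side.** Pointing to treatment only: the section heading, the last listed reason (the investigator may stop intervention) and the closing rule's reference to stopping treatment. Pointing to trial exit: the lead sentence, the recorded withdrawal date, the shared list with consent withdrawal and loss to follow-up, and the one assessment described as final. No sentence in the article says that visits continue after treatment stops, and none orders them to stop.

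**2. Visits at stake, on the trial-exit reading only.** There are four post-baseline VAS visits. Exit before day 10 forgoes 4 of 4, between days 10 and 20 3 of 4, between day 20 and 1 month 2 of 4, and between 1 and 3 months 1 of 4. An exit VAS may be obtained, but not at a scheduled time.

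**3. The plan's own figure on outcome loss (Sample size).** 33 / (1 − 0.20) = 41.25, so 42 per group, and 3 × 42 = 126. This reproduces. The 20% allowance is not split by reason or by arm.

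**4. Size of a possible bias.** Let p be the share of an arm that exits, and d the amount by which the mean unseen VAS differs from its imputed mean. The bias in a pairwise difference is p(control) × d(control) − p(YLDJJ) × d(YLDJJ). With a common d it is (p(control) − p(YLDJJ)) × d. All p and d are assumptions.

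| Exit share, YLDJJ vs control | d = 0.5 | d = 2.0 |
|---|---|---|
| 10% vs 10% | 0 | 0 |
| 5% vs 10% | 0.025 | 0.10 |
| 5% vs 15%, or 10% vs 20% | 0.05 | 0.20 |
| 0% vs 20% (extreme) | 0.10 | 0.40 |

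Against the 1.5-point target, 0.20 is 13% and 0.40 is 27%. With SD 1.8 and 33 per group, SE = 1.8 × √(2/33) = 0.443, so 0.20 is 0.45 SE and 0.40 is 0.90 SE. A bias of 0.20 would take a nominal 5% test to 7.4% if it inflates the effect, or cut power for 1.5 points from 92.3% to 83.5% if it dilutes it. For 0.40 the figures are 14.7% and 69.9%.

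**5. Direction.** Suppose more people exit from the control arm. If their pain stays worse than imputed, d is positive and the YLDJJ advantage is understated. If the prohibited treatment works and their pain falls below the imputed value, d is negative and the advantage is overstated.

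**6. A pain-triggered version, by simulation.** Assumptions: 42 per arm, SD 1.8, true day-20 difference 1.0 to 1.5, correlations 0.6 to 0.8. Half of those whose pain exceeds 6.5 to 7.5 between days 10 and 20 are removed, with the same threshold in both arms. Imputation uses group, baseline and day 10. Exits are then 4–10% of sham and 1–5% of YLDJJ. The day-20 difference shrinks by 0.02 to 0.06 if the other treatment has no effect, and moves by no more than about 0.02 if it lowers pain by 1 point. With everyone above the threshold removed (8–20% of sham), the shrinkage reaches 0.15.

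**7. Would the planned checks reveal it?** In the half-removed setting, complete-case and imputed day-20 differences lie on average only 0.01 to 0.02 apart (SD between trials 0.03 to 0.04). Both PP definitions need the day-20 VAS, so those who exit before it are absent there too. Agreement between these analyses would not show that the loss was harmless.

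**The case against.** The milder reading has real support. The heading and two other phrases speak of treatment, Table 4 records additional treatment at all four later visits, and eligibility violations are already handled by PP exclusion. Exit is also discretionary. The source is a journal article, which may leave procedures after discontinuation to the full protocol. All of this stands, and it is why the fault is contradictory wording and not an order to stop follow-up. It does not remove the point. The lead sentence and the single final assessment are stated text, and a site could reasonably act on them.

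Several stronger readings are tempting but unsupported:
- That these participants drop out of ITT. They stay in, and their missing values are imputed.
- That three of four VAS values are certain to be lost. That holds only on the trial-exit reading and for exits between days 10 and 20.
- That the planned checks always miss these people. Someone who exits after day 20 already has the value that PP requires.
- That the bias is known to be large, known to be small, or known in direction. The article gives no exit rate. The simulation also leaves out rescue medication, which the plan records and models.
- That the Risk–benefit assessment confirms removal of individuals, where it says "the researchers may discontinue the trial when necessary based on combination therapy/medication rules and discontinuation/withdrawal criteria". That sentence can mean halting the whole trial, and its stated purpose is participant protection.

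**Conclusion.** The point holds as a wording fault with a consequence for data collection. Read as trial exit, the section permits pain-related loss of primary-outcome values, which conflicts with the ITT aim and with the Additional treatment item in Table 4. For exits before day 20, the planned checks would not expose it.

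The size is an assumption throughout. Exit shares 5 to 10 percentage points apart, with unseen values 0.5 to 2 points off, give about 0.03 to 0.2 VAS points. Equal shares and departures give none. Only the extreme case, with the whole 20% allowance falling in one arm, reaches 0.4. The sign is open. The case for acting is that the loss cannot be undone while the correction is cheap. It should be made, but the trial does not stand or fall on it. Late-found ineligibility adds little and is not quantified.

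**What to change.** Reword Criteria for discontinuation of the intervention to say:
- Starting a prohibited treatment, or ineligibility found after randomisation, may stop the study intervention and must stop it where safety requires, but does not end follow-up.
- VAS and every other assessment that remains safe continue at all remaining scheduled visits unless the participant withdraws consent to follow-up. Resting-state fMRI is omitted where MRI is contraindicated. This exception is needed because Table 4 schedules fMRI at every visit, and the exclusion criteria include "Presence of implanted metal or electronic medical devices, such as cardiac pacemakers, a history of epilepsy, or intracranial hypertension".
- The prohibited treatment and its date are recorded under the existing Additional treatment item, and the observed VAS values are used in the primary ITT model.

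The Risk–benefit assessment needs no change. The cost is an amendment with the approvals and registry update that the article requires for any protocol modification. Visits and the recording item already exist, and N stays at 126. One downside remains: some VAS values will be measured under other pain treatment and must be flagged.
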